### Procedure

The study will run from September 2022 until January 2025. Data will primarily be collected at the participating schools, however interviews with parents and school staff may take place over the phone, via internet video call, at participants’ homes, or in another location of the participant’s convenience. Baseline length will be one school term. During the baseline phase, the teacher will provide repeated measures of the primary quantitative outcomes: participating children’s ADHD symptoms and classroom functioning. These will be collected every 2 weeks during the baseline period and in the intervention period. This detailed baseline data will capture normal fluctuations in symptoms across the term and response to any school-implemented ‘treatment as usual’ during the baseline phase.

Information on healthcare and education resource use will be collected from children, parents and school staff for each child during the baseline period using a structured survey with open questions to capture any resources not mentioned, and child quality of life will be reported by the child and their parent. Any other support or treatment will not be altered during the study. Each school will then implement the intervention for one school term; two modules from the intervention will each be implemented for 4 weeks. There will be a 10-week follow-up period where detailed qualitative data will also be captured, including asking participants about changes in resource and service use relative to the information they provided at baseline.

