## Methods and analysis

### Design

A randomised iterative mixed-methods case-series design will be used. Schools will be the units of randomisation, and will be randomised to the time (school term) when they will use the toolkit. The toolkit will be refined after each school has used it for one term, or more frequently if major issues are highlighted during a school’s use of the toolkit. Small, theory-based and data-driven changes hypothesised to be relevant across the school context will be made, as well as reactive changes addressing barriers to implementation. Randomisation to using the toolkit in different school terms allows for inferences to be made as to whether the intervention is improving outcomes, with consistent improvement following the introduction of the core components enabling researchers to potentially rule out alternative explanations for behaviour change, such as improvement due to other support in place or differences in behaviour across the school year. If baseline symptoms and functioning remain on stable trajectories for children across schools, changing only when the intervention is introduced, this implies it is the intervention rather than an alternate factor stimulating the change. It is a commonly used design for single-subject analyses where the intervention cannot be withdrawn and re-implemented such as in an ABAB design.^25–27^

Eight schools will participate in total in two recruitment cohorts of four (in order to avoid later participating schools having to sign up to the study years in advance); each cohort will enter the study at a different time. Schools in each cohort will then be randomly assigned their individual baseline term in the study using a computerised random sequence generator (see figure 1). The length of the baseline period will be the same for each school (one school term), with schools within each cohort entering their baseline period in different school terms; the term in which the intervention is delivered is therefore staggered across the study (figure 1). This design will allow for refining and adapting the toolkit and its implementation based on ongoing participant feedback, maximising the chances it has of being acceptable and feasible (and therefore suitable for further evaluation in a pilot and then definitive cluster randomised controlled trial) by the end of the study.

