**Toolkit steps**																																							
Know ADHD											X	X	X																										
Know me											X	X	X																										
Understand motivations and develop targets													X	X	X																								
Establish digital school-home notebook														X	X																								
Map targets to modules and choose strategies														X	X																								
Implement strategies (module 1)															X	X	X	X	X	X																			
Implement strategies (module 2)																					X	X	X	X	X	X													
Study measures (data collection)																																							
Measures of ADHD symptoms	X		X		X		X		X		X		X		X		X		X		X		X		X		X			X			X			X			X
Measures of classroom functioning	X		X		X		X		X		X		X		X		X		X		X		X		X		X			X			X			X			X
Toolkit iteration feedback (qualitative)																		X								X													
Process evaluation: fidelity, acceptability, perceived usefulness																											X	X	X	X	X	X	X	X	X	X			
Child dimensional psychopathology and school functioning	X											X							X							X											X		
Child-reported satisfaction with school	X											X							X							X											X		
Teacher well-being	X											X							X							X											X		
Healthcare and education resource use	X											X															X												X
Child quality of life	X											X															X												X

Online supplemental material contains information on the Toolkit steps. Measures are: ADHD symptoms: the Strengths and Weaknesses of ADHD and Normal Behavior Scale (SWAN); Classroom functioning: problem behaviour subscale of the Social Skills Improvement System (SSIS); Dimensional psychopathology and school functioning: the Strengths and Difficulties Questionnaire and the academic competence and social skills subscales of the SSIS; Satisfaction with school: the How I Feel About My School Questionnaire; Teacher well-being: the Warwick‐Edinburgh Mental Well-Being Scale 14-item Teacher Survey, and the Relationship with Work survey from the Maslach Burnout Inventory- General Survey, and the Teacher Sense of Efficacy Scale; healthcare and education resource use is a bespoke questionnaire available from the authors on request; and Child quality of life is measured by child-report and parent proxy Child Health Utility-9D.

ADHD, attention deficit/hyperactivity disorder.

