##### Subaim C

Assess whether measures of behaviour, classroom functioning and teacher-reported ADHD symptoms indicate improvement following use of the toolkit. *To explore whether there is indication that the toolkit may be efficacious*, quantitative data will be visually analysed within schools and participants, describing the nature of change over time and in relation to the intervention, following recommendations.^31^ Non-parametric analysis of the data will be considered, for example, by calculating Tau-U statistics. As the toolkit will be refined between schools participating, it would be irrelevant to compare measures across individuals who received different iterations of the toolkit; the focus will therefore be on assessing whether there is initial indication of improvement in outcomes, and whether any effect is replicated across individuals. Comparisons between the magnitude of change seen between those who receive earlier and later iterations of the toolkit will be carried out as it is anticipated that later iterations, modified to be more acceptable and feasible, would result in greater evidence of behaviour change. This will be an exploratory analysis. The core and target behaviours chosen across study participants will also be explored in a descriptive manner in order to assess the use of the behaviour web, targets and modules.

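### Table 3 starts toolkit steps in weeks 11–13 of a term the text treats as pre-intervention, so two of seven baseline ratings and the whole week-12 assessment may be exposed

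*Protocol article*

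**What the plan says.** The Procedure section fixes the phases by term: "Baseline length will be one school term". Of the teacher ratings of ADHD symptoms and classroom functioning it says "These will be collected every 2 weeks during the baseline period and in the intervention period". It gives their baseline purpose as "This detailed baseline data will capture normal fluctuations in symptoms across the term", together with response to treatment as usual, and continues: "Each school will then implement the intervention for one school term". It mentions no toolkit activity during baseline.

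The Design section rests its inference on baselines that stay stable until the intervention is introduced, "with consistent improvement following the introduction of the core components enabling researchers to potentially rule out alternative explanations for behaviour change".

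Table 3 reads differently. Under its toolkit steps, Know ADHD and Know me are marked in baseline weeks 11, 12 and 13 and nowhere else. The step "Understand motivations and develop targets" is marked in baseline week 13 and intervention weeks 1 and 2. Classroom strategies (module 1) begin in intervention week 2.

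For analysis, Subaim C plans visual inspection within schools and participants, and adds: "Non-parametric analysis of the data will be considered, for example, by calculating Tau-U statistics". It names no week at which the baseline phase ends.

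**The concern.** A staggered-baseline design depends on knowing which observations came before the intervention. The text draws that line at the end of the term, whereas Table 3 has the toolkit under way about three weeks earlier. Ratings from those weeks are then presented as ordinary fluctuation when they may not be.

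Two things are at stake. The first is the within-child comparison in Subaim C. Any early response would be counted as baseline. It would also look like a baseline trend, which a trend-corrected Tau-U subtracts a second time.

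The second is the end-of-baseline assessment in week 12: psychopathology and school functioning, school satisfaction, teacher well-being and efficacy, resource use, and quality of life. With week 12 possibly exposed, week 1 is the only unexposed value. The change from week 1 to week 12 can no longer be read as pure baseline drift, and the week-12 resource survey could absorb time spent on training. Fortnightly ratings can be relabelled later, but an unexposed late-baseline value that was never collected cannot be recovered.

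**Working it through.** **Schedule (Table 3, 3 terms × 13 weeks = 39 columns)**

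| Row | Weeks marked |
|---|---|
| Know ADHD; Know me | baseline 11, 12, 13 |
| Motivations and targets | baseline 13; intervention 1, 2 |
| Strategies, module 1 | intervention 2–7 |
| ADHD symptoms; classroom functioning | baseline 1, 3, 5, 7, 9, 11, 13; intervention 2, 4, 6, 8, 10, 12 |
| End-of-baseline secondary, resource-use and quality-of-life sets | baseline 12 (first taken in baseline 1) |

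The stated frequency is reproduced: every 2 weeks from week 1 of 13 gives 7 baseline ratings. Two of the 7 (29%) fall in toolkit weeks and 5 do not.

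**Assumptions (not in the protocol).** Ratings are independent and normal with within-child SD 1. The toolkit effect *d* is present in full at all 6 intervention ratings. A share *f* of it is already present at baseline weeks 11 and 13.

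**Phase-mean difference.** The multiplier is 1 − (2/7)*f*: 0.93, 0.86 and 0.71 at *f* = 0.25, 0.5 and 1. If only week 13 is in effect exposed, it is 1 − (1/7)*f*: 0.96, 0.93 and 0.86.

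**Tau.** For two ratings whose means differ by *x* SD, the expected pair score is t(*x*) = 2Φ(*x*/√2) − 1, so t(1) = 0.5205. There are 7 × 6 = 42 baseline–intervention pairs: 30 involve the five clean ratings and 12 the two exposed ones.

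- Tau = [30·t(*d*) + 12·t((1−*f*)*d*)]/42
- Trend-corrected Tau-U subtracts the 5 × 2 = 10 clean-versus-exposed baseline pairs: [30·t(*d*) + 12·t((1−*f*)*d*) − 10·t(*fd*)]/42

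Example at *d* = 1, *f* = 0.5, with t(0.5) = 0.2763: Tau = (15.615 + 3.316)/42 = 0.45; Tau-U = (15.615 + 3.316 − 2.763)/42 = 0.38.

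| *f* (at *d* = 1) | Tau | Trend-corrected Tau-U |
|---|---|---|
| −0.5 | 0.58 | 0.64 |
| −0.25 | 0.55 | 0.58 |
| 0 | 0.52 | 0.52 |
| 0.25 | 0.49 | 0.45 |
| 0.5 | 0.45 | 0.38 |
| 1 | 0.37 | 0.25 |

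Negative *f* means that the early steps raise reported symptoms. With only the five clean ratings, both statistics are 0.52 for every *f*.

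**Cost of dropping two points.** This is the simulated chance of an exact two-sided rank-test p < 0.05 for one child at an assumed *d* = 2. Five clean ratings against six give about 0.72. All seven against six give about 0.84, 0.78, 0.67 and 0.36 at *f* = 0, 0.25, 0.5 and 1. The two options cross at roughly *f* = 0.4.

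**Secondary set.** A change measured from week 12 alone is multiplied by 1 − *f*.

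**The case against.** The strongest reply is that the weeks 11–13 steps are, by name, knowledge and preparation. Notebook set-up and strategy choice fall in intervention weeks 1–2, and no classroom strategy is used until intervention week 2. The Intervention description ties support for the child to strategies that change the environment and expectations. Child ratings may therefore barely move before the phase boundary, and week 11, as the first contact week, may be effectively unexposed. This stands, and it is why the size is given as a range that includes no effect.

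A reader might infer that the phase comparison is biased towards no change. The documents do not support that as an unconditional statement. It requires the early steps to improve ratings, and the protocol gives no size for such an effect. Teachers are the raters, and learning about ADHD could make them report more symptoms, which would exaggerate later improvement.

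A reader might also infer that the core components are introduced inside the baseline phase. The Introduction describes core components followed by optional modules, which makes that reading natural, but no section maps core components to Table 3 rows. Nor is a phase line at first toolkit contact excluded, because Subaim C fixes no cut-point and only considers Tau-U. That weakens any charge against a specific analysis. It does not remove the conflict between Table 3 and the Procedure section.

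Two further points hold. The secondary set does have an unexposed value, in week 1. And the study is explicitly not powered and does not aim to assess effectiveness; progression depends on feasibility criteria and qualitative data, none of which uses the phase contrast.

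**Conclusion.** The scheduling conflict is certain: two of seven baseline ratings and the whole week-12 set fall in weeks marked for toolkit steps, within a term the text describes as pre-intervention. The consequence is conditional. Under independent ratings and an assumed 1-SD effect, Tau ranges from 0.52 (no early effect) down to 0.37 (full effect by week 11, an extreme case), and trend-corrected Tau-U from 0.52 down to 0.25. If training raises teacher-reported symptoms, both exceed 0.52.

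The case for separating weeks 11–13 is validity of the baseline, not power: five points are the more sensitive choice only if about 40% or more of the effect precedes any strategy. The damage is confined to Subaim C, an exploratory secondary aim, and to the baseline resource-use data behind Subaim B. The two main feasibility aims are untouched. Severity is minor to moderate. It is worth acting on because the remedy is cheap and the late-baseline secondary values cannot be recovered afterwards.

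**What to change.** 1. Move the week-12 secondary, resource-use and quality-of-life assessments to baseline week 10, before the first toolkit step in Table 3.
2. State in Subaim C that the clean baseline is weeks 1–9 (five ratings). Mark weeks 11–13 as a separate preparatory phase in the plots, and report any Tau-U both without and with the ratings from weeks 11 and 13.
3. Reconcile Table 3 with the Design and Procedure sections, so that baseline has one meaning, and say which Table 3 steps are the core components on which the inference rests.

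The cost is one column shifted in Table 3 and a few sentences of text. The statistical price is five rather than seven clean baseline points, which lowers per-child sensitivity if the early steps have little effect (about 0.72 against 0.84 at an assumed *d* = 2). Reporting the result both ways keeps that information in view.

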### Intervention delivery

The intervention is currently in development. Broadly, it will take the form of a digital toolkit of training and resource packages and behavioural strategies for non-specialists to use, organised within ‘modules’ that cover different classroom-based problems common to ADHD: we anticipate that each child participant will receive two modules. SENCos will have the role of coordinating and supporting teachers and TAs to deliver the toolkit in conjunction with support from parents at home, and given agency over the duration, dose and discontinuation of strategies. Online supplemental figure 1 illustrates the participant structure and roles within a school (see online supplemental material).

### Intervention description

The Tools for Schools *FLEX* toolkit will primarily be a digital resource. The current logic model is shown in figure 2 and the toolkit outline is shown in the supplemental material (online supplemental figure 2). The key goals of the toolkit that will foster sustainable behaviour change are to:

*Understand* the child and their communications*Adapt* the classroom and school expectations*Support* the child to:reduce acute impairmentsincrease skillsimprove self-identity through providing strategies that change the environment and expectations around the childThis results in the child being able to consciously monitor and self-regulate.*Sustain* and adapt across time.

**Figure 2 F2:**
[figure not shown]
Intervention draft logic model. ADHD, attention deficit/hyperactivity disorder.

Table 3 shows the data collection schedule relative to the stage within the study. A full intervention description can be found in the online supplemental material.

**Table 3 T3:** Data collection schedule and toolkit implementation timeline

School terms	Baseline term													Intervention term													Follow-up term												
Week	1	2	3	4	5	6	7	8	9	10	11	12	13	1	2	3	4	5	6	7	8	9	10	11	12	13	1	2	3	4	5	6	7	8	9	10	11	12	13
**Toolkit steps**																																							
Know ADHD											X	X	X																										
Know me											X	X	X																										
Understand motivations and develop targets													X	X	X																								
Establish digital school-home notebook														X	X																								
Map targets to modules and choose strategies														X	X																								
Implement strategies (module 1)															X	X	X	X	X	X																			
Implement strategies (module 2)																					X	X	X	X	X	X													
Study measures (data collection)																																							
Measures of ADHD symptoms	X		X		X		X		X		X		X		X		X		X		X		X		X		X			X			X			X			X
Measures of classroom functioning	X		X		X		X		X		X		X		X		X		X		X		X		X		X			X			X			X			X
Toolkit iteration feedback (qualitative)																		X								X													
Process evaluation: fidelity, acceptability, perceived usefulness																											X	X	X	X	X	X	X	X	X	X			
Child dimensional psychopathology and school functioning	X											X							X							X											X		
Child-reported satisfaction with school	X											X							X							X											X		
Teacher well-being	X											X							X							X											X		
Healthcare and education resource use	X											X															X												X
Child quality of life	X											X															X												X

Online supplemental material contains information on the Toolkit steps. Measures are: ADHD symptoms: the Strengths and Weaknesses of ADHD and Normal Behavior Scale (SWAN); Classroom functioning: problem behaviour subscale of the Social Skills Improvement System (SSIS); Dimensional psychopathology and school functioning: the Strengths and Difficulties Questionnaire and the academic competence and social skills subscales of the SSIS; Satisfaction with school: the How I Feel About My School Questionnaire; Teacher well-being: the Warwick‐Edinburgh Mental Well-Being Scale 14-item Teacher Survey, and the Relationship with Work survey from the Maslach Burnout Inventory- General Survey, and the Teacher Sense of Efficacy Scale; healthcare and education resource use is a bespoke questionnaire available from the authors on request; and Child quality of life is measured by child-report and parent proxy Child Health Utility-9D.

ADHD, attention deficit/hyperactivity disorder.

### Qualitative data collection

#### Toolkit iteration feedback

The toolkit will go through several iterations, refined based on ongoing data collection and analysis. Flexibility allowing for this is a strength of the study design.^31^ Brief semistructured ‘feedback sessions’ will be held by phone or in person with all participating school staff and parents during the intervention period, in order to understand where modifications need to be made to the design, content and measures of the intervention. Example questions from the topic guide for teachers are included in the online supplemental material. All changes made from the original prototype of the toolkit will be recorded in a change log, including the reason for the change, when the change was made and what aspects of the toolkit the change relates to. The planning group and the study advisory group will convene to discuss feedback or major suggested modifications, and to review minor changes in the change log.

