#### Process evaluation

During the 10-week follow-up period, detailed qualitative data will be collected to assess acceptability, perceived usefulness, fidelity and implementation of the intervention, exploring in more depth what participants did and did not do and explanations of their actions, with questions similar to those shown above. Focus groups comprising the constellation of all school staff involved with one child will be held for all participants. This format is familiar to school staff as professional discussions often take a ‘case conference’ format. Interviews by phone or an online platform such as zoom will be conducted with a purposive sample of half of the parents, using the same criteria detailed above (ie, at least 50% from areas with a deprivation index above the regional mean) and aiming to attain a balance of male and female parents. Children will take part in ‘active interviews’ during the process evaluation in the follow-up period with a researcher (at home or at school), where they will have an informal conversation about their experiences of the study, if they recalled any new things their teacher tried with them, how they felt about their behaviour targets (if they knew about them), and how they found the research process.

All children will be invited to an activity- based interview with the option of a paired interview, where they can bring an accompanying family member of their choosing. Paired interviews can reduce stress, mitigate child protection risks and reduce issues of running a focus group where children in the school with traits of ADHD are identified to one another. The activity interviews will be designed with the planning group and piloted with children with ADHD, for example, these may involve collecting objects of different colours or taking photos around the school to represent answers to questions (such as *can you show me where you like to go if you feel you need to calm down? What are your favourite things about school? What do you not like about school?*), and using these objects or photos as prompts to discuss thoughts.

All participants in the process evaluation will be asked what they think the most important outcome would be for a future hypothetical trial of the toolkit, and why.

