#### Adverse effects of intervention

It is possible that the intervention will lead to adverse effects or negative impacts on participating children, such as feeling singled out due to the intervention leading to social exclusion from the peer group.^32^ The study planning group will contribute to identifying potential adverse effects (*as of 21 March social exclusion is the most prominent concern*), and qualitative data will be collected from participants at the feedback and process evaluation stages to assess perceptions of negative impacts of the intervention. Modifications will be made as needed in relation to this through consultation with the planning group and the academic advisory team.

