### Quantitative measures

There are two quantitative outcome measures that will be assessed in order to: (1) Determine which would be most suitable as the primary outcome in a future trial and (2) Evaluate whether they make sense and are relevant to those completing the measures. *ADHD symptoms* will be measured using the Strengths and Weaknesses of ADHD Symptoms and Normal‐behavior Questionnaire, based on preferences of the planning group who considered several measures of ADHD symptoms,^33 34^ reported by teachers; and *classroom functioning problem behaviour* subscale measured using the Social Skills Improvement System (SSIS),^35^ that captures social, academic and competing problem behaviours in the classroom environment, reported by parents and teachers. These will be measured every 2 weeks during the baseline and intervention periods and every 3 weeks during the follow-up period. All planned quantitative measures are detailed in a table in the online supplemental material.

Other quantitative measures will be captured to assess whether there is indication of some improvement in the key areas the toolkit aims to target. Measures relating to children include *child dimensional psychopathology*, assessed using the teacher and parent-reported Strengths and Difficulties Questionnaire,^30^ and *child-reported satisfaction with school* using the How I Feel About My School measure.^36^
*Teacher well-being* will be measured using the Warwick‐Edinburgh Mental Wellbeing Scale 14-item Teacher Survey^37^ the Teachers’ Sense of Efficacy Scale,^38^ and the Relationship with Work Survey from the Maslach Burnout Inventory-General Survey,^39 40^ and the social skills and academic competence subscales from the SSIS will be completed by teachers. These will be collected at the beginning and end of the baseline period, at the end of the intervention term and at the end of the follow-up term. Other module-specific measures which are not covered by the above measures will be administered depending on the modules used by each child, for example, the Harter Self-Perception Profile for Children to measure self-esteem.^41^

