## Ethics and dissemination

### Ethics and governance approval

Ethical approval has been awarded by the University of Exeter College of Medicine and Health Research Ethics Committee (Ref Jan22/B/300). Informed consent will be sought from all adult participants (and by parents for child participants; an example information sheet and consent form are provided in the online supplemental material). Children will provide assent and ongoing assent will be judged by the research team throughout. Should it become clear that a child does not want to continue to participate in data collection or the study, withdrawal will be discussed with parents and school staff. Should a child express that they wish to stop during a single instance of data collection, this will be stopped for that day. The child’s feelings will be respected and discussed with the child, their parents and school staff about their future involvement. Ultimately, decisions will be made in line with the best interests of the child. All data collected will comply with General Data Protection Regulations, being stored on secure servers and only accessible by the research team. Some data will be shared as part of the intervention, for example, teachers’ ratings of ADHD symptoms will be viewable by the SENCo and express permission will be sought for any planned data sharing between participants. Participants will be asked whether their data can be made available following the study for future analysis or related research. Those that consent will contribute their data to a fully anonymised data set accessible to bona fide researchers. There are several operational issues and associated risks that are involved in performing this study. It is possible that the intervention will lead to adverse outcomes^32^ such as study children feeling singled-out from their peers due to the intervention. The planning group will discuss anticipated potential adverse outcomes due to the intervention, and qualitative feedback will be sought from participants both during their use of the intervention and in the follow-up period. Further risks (aside from those detailed in progression criteria in table 2) have been identified and mitigation plans detailed, as well as key study limitations noted (see online supplemental material).

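### Adverse-effect feedback is promised from participants during use of the toolkit, but the in-term sessions list only staff and parents, and children are interviewed after both modules have ended

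*Protocol article*

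**What the plan says.** The section on adverse effects of the intervention gives as its example a child "such as feeling singled out due to the intervention leading to social exclusion from the peer group", and ranks social exclusion as the leading concern at the time of writing. It says that "qualitative data will be collected from participants at the feedback and process evaluation stages to assess perceptions of negative impacts of the intervention", and that the toolkit will be modified as needed in response. The ethics and governance section repeats the commitment: "qualitative feedback will be sought from participants both during their use of the intervention and in the follow-up period". The recruitment section lists eligible children among the study participants.

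The section on toolkit iteration feedback defines the feedback stage. Its sessions are held "with all participating school staff and parents during the intervention period", and their purpose is given as "in order to understand where modifications need to be made to the design, content and measures of the intervention". Children are not in that list. The process evaluation section places the children's interviews in the follow-up period. The topics it mentions include "how they felt about their behaviour targets (if they knew about them), and how they found the research process"; being singled out or excluded is not among them.

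On child-completed measures, the quantitative measures section has school satisfaction collected at the start and close of baseline and then "at the end of the intervention term and at the end of the follow-up term". Table 3 adds a further collection in intervention week 6.

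**The concern.** Feeling singled out is first of all the child's own experience. Adults may see its outward signs, such as a child left out by peers, but the child is the direct source. Two sections can be read as saying that source is used while the toolkit is in use. The section that sets up the in-term sessions does not include it.

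Timing matters because the plan ties harm reports to modification. The design section refines the toolkit after each school's term, or sooner if major problems emerge during use. A report that first reaches the team in the follow-up term cannot lead to any change while that child is still receiving the toolkit. This applies to every child participant, 16 to 32 by the plan's own range.

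**Working it through.** No sample size or error rate bears on this point. The check is a reading of Table 3 by column (39 weeks, 13 in each of the baseline, intervention and follow-up terms), set beside the text.

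**Positions in Table 3**
- Module 1: intervention weeks 2 to 7. Module 2: intervention weeks 8 to 13.
- Toolkit iteration feedback: intervention weeks 5 and 13.
- Process evaluation, which contains the child interviews: follow-up weeks 1 to 10.
- Child-reported school satisfaction: baseline weeks 1 and 12, intervention weeks 6 and 13, follow-up week 11.
- Child quality of life: baseline weeks 1 and 12, follow-up weeks 1 and 13.

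**Delay to the child interview.** Number the weeks from the first week of the intervention term, so that follow-up week k is week 13 + k.
- Earliest: 13 + 1 = 14, and 14 − 2 = 12 school weeks after module 1 starts.
- Latest: 13 + 10 = 23, and 23 − 2 = 21 school weeks after module 1 starts.
- Relative to the last week of module 2: 14 − 13 = 1 to 23 − 13 = 10 school weeks after it.

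By comparison, the staff and parent sessions fall 5 − 2 = 3 and 13 − 2 = 11 weeks after module 1 starts. The Procedure section gives each module four weeks where Table 3 shows six. Under either figure both modules are delivered within the intervention term, so the order does not change.

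**Scheduled child self-report in the intervention term.** The only such row in Table 3 is the school-satisfaction questionnaire, in weeks 6 and 13. It is described as satisfaction with school and not as a harm measure. Some module-specific self-report, such as a self-perception profile, may also be given, but this depends on the modules chosen. Assent monitoring concerns willingness to continue.

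**What each questionnaire date could achieve.** After week 6, weeks 7 to 13 remain: 13 − 6 = 7 weeks of delivery, one of module 1 and six of module 2. Week 13 is the final delivery week. Answers given then can inform the end-of-term refinement, but not that child's own experience. The disagreement between the quantitative measures text and Table 3 over week 6 therefore decides whether an existing child contact falls early enough to be useful to that child.

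**The case against.** The strongest reply is that this is a defensible design choice with no strict contradiction. The feedback section says who attends without saying that nobody else is asked, and a promise about participants in general is met if some of them are asked during use. The planning group, which includes nine children with ADHD, weighed participant burden. Topic guides and risk mitigation plans are in a supplement that is not shown and may contain child questions. Asking children aged 4 to 10 about being singled out could itself make them feel so. These points rule out calling the passages irreconcilable, and the caution about wording stands. They do not remove the ambiguity: the article's one description of the feedback stage names adults only, and it places the child interviews in follow-up.

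Three stronger readings are tempting and are not supported.

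- A reader might infer that harm goes unmonitored during the term. It does not. Staff and parents are asked in weeks 5 and 13, researchers observe classrooms, social-skills ratings are scheduled, and signs of distress or reluctance are watched for. Peer exclusion is at least partly visible to adults.
- A reader might infer that nothing can be changed for an affected child. That would hold only if the child were the sole source of the signal. The plan allows earlier refinement and gives school coordinators latitude over the strategies.
- A reader might infer that the next school is already using the same content. Figure 1 is not shown, so the spacing between schools is unknown, and the toolkit is due for refinement after each school's term. If the spacing were one term, follow-up week 1 would be the next school's intervention week 1. Table 3 starts strategies in week 2, so the earliest interviews could still inform that school, while those in follow-up weeks 2 to 10 would come after its strategies had begun.

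**Conclusion.** The point holds in a limited form. The sections on adverse effects and ethics, read with the list of participants, imply that children are asked about harm during use. The feedback and process evaluation sections describe no such contact. As written, the child's own account of the named harm first arrives 12 to 21 school weeks after module 1 starts and after both modules have ended, which is too late to inform changes for that child. Any effect on later schools is conditional on the stagger. The mismatch over the week-6 measures is a separate inconsistency, relevant here because it affects the most useful child contact.

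This rests on the dates in Table 3 and on the article text, without sight of the supplement. It is a correctable weakness in detecting a harm the plan itself identifies. It does not undermine the main feasibility aims.

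**What to change.** 1. Reconcile the toolkit iteration feedback section with the adverse effects and ethics sections, so that all three say the same about whether children are asked during the intervention.
2. Reconcile the quantitative measures section with Table 3 on whether the week-6 measures are collected.
3. Add one or two neutral, age-appropriate items on feeling left out or treated differently, worded with the planning group, to the child questionnaire already scheduled in the intervention term: week 6 if that collection is kept, and week 13. If week 6 is dropped, the items serve the end-of-term refinement but not the responding child.
4. Pass the answers to the planning and advisory groups, and record any resulting change in the existing change log.

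No new data collection point, staff or sample size is needed if week 6 stands. The cost is a little more child time, and care that the wording does not itself make a child feel singled out.
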